## Abstract

**Introduction:**

The use of marginal or extended criteria donor livers is increasing. These organs carry a greater risk of initial dysfunction and early failure, as well as inferior long-term outcomes. As such, many are rejected due to a perceived risk of use and use varies widely between centres. Ex situ normothermic machine perfusion of the liver (NMP-L) may enable the safe transplantation of organs that meet defined objective criteria denoting their high-risk status and are currently being declined for use by all the UK transplant centres.

**Methods and analysis:**

Viability testing and transplantation of marginal livers is an open-label, non-randomised, prospective, single-arm trial designed to determine whether currently unused donor livers can be salvaged and safely transplanted with equivalent outcomes in terms of patient survival. The procured rejected livers must meet predefined criteria that objectively denote their marginal condition. The liver is subjected to NMP-L following a period of static cold storage. Organs metabolising lactate to ≤2.5 mmol/L within 4 hours of the perfusion commencing in combination with two or more of the following parameters—bile production, metabolism of glucose, a hepatic arterial flow rate ≥150 mL/min and a portal venous flow rate ≥500 mL/min, a pH ≥7.30 and/or maintain a homogeneous perfusion—will be considered viable and transplanted into a suitable consented recipient. The coprimary outcome measures are the success rate of NMP-L to produce a transplantable organ and 90-day patient post-transplant survival.

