## Statistical justification and outcome analysis

### Sample size justification

For (A) feasibility of NMP-L to rescue discarded liver grafts, it is anticipated that NMP-L will achieve a desirable organ recovery rate of at least 50%, with an undesirable rate of 30% or less as this would not be considered economically feasible. The significance level (α) is set at 0.05, corresponding to the probability of incorrectly rejecting the hypothesis given it is true (type I error), and the power is set at 0.90 (type II error rate, β=0.10), corresponding to the probability of correctly deciding the NMP-L treatment is successful given the true response rate is greater than 50%.

Using a Simon’s two-stage design^38^:

Interim assessment stage 1A of accrual: 24 marginal grafts will be perfused and assessed in the first stage. Grafts will be transplanted depending on the criteria achieved. The procedure will be considered infeasible if there are fewer than eight recovered livers. If more than eight livers are transplanted, we will proceed to Stage 2A.

Final stage 2A of accrual: Up to additional 29 marginal grafts will be perfused. We would consider the procedure feasible if there are at least 22 recovered livers out of 53 perfused livers.

For (B) for viable livers transplanted following NMP-L, a desirable 90-day patient survival rate is at least 88%, with an undesirable rate of 73% (15% lower). The mean 90-day patient survival rate for ‘standard’ liver transplants is 93%.^42^ An optimal three-stage design^39^ will be used to test the null hypothesis that the mean 90-day patient survival rate will be less than 73% (p≤0.73) versus an alternative hypothesis that the 90-day patient survival rate will be at least 88% (p≥0.88). The significance level is set at 0.20 (target α=0.2), giving a 0.2 probability to conclude that a single transplantation is viable when it truly is not viable. The power is set at 80% (target β=0.2), giving a 0.2 probability to conclude that a single transplantation is not viable when it truly is viable.

Interim assessment stage 1B: Following transplantation in three patients, the trial will stop early (concluding p≤0.73) if there are fewer than two patients achieving 90-day survival. If two or more patients reach the primary end point of 90-day survival, an additional eight transplantations will be performed.

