#### Secondary analysis

For all secondary outcome measures, analyses will be mainly descriptive. Continuous exploratory measures will be summarised via means, medians, SD and ranges. Categorical measures will be summarised with number and proportion in each category. To model repeated measures over time (eg, QoL), a linear mixed effects model (considering subject correlation) using parametric and more flexible models may be considered. Time-to-event outcomes will be assessed using the method of Kaplan and Meier. Median survival with corresponding 95% CI will also be reported where appropriate. The assessment of graft function post-transplantation by incidence of primary non-function and early allograft dysfunction will be carried out by comparing results with a contemporary matched recipient group of patients obtained from a prospectively maintained database, with adjustment for potential confounders.

The contemporary matched recipient group will be matched using the following:Patient characteristics: age, sex, BMI, model for end-stage liver disease (MELD), UK end-stage liver disease (UKELD), aetiology;Donor liver characteristics: DCD or DBD, sex.

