### Recipient inclusion criteria

Suitable potential VITTAL graft recipients will be identified during the listing process. Patients will be told that they are potentially suitable to receive a graft from the VITTAL trial and will be given the patient information sheets to read more about the trial. If already listed, potential recipients will be identified on the list, contacted and sent the same documentation. If they wish to take part, a minimum of verbal consent will be taken. Enrolling in the trial will in no way impact on the chance of them receiving a standard ‘transplantable’ graft. Patient’s with all aetiologies of chronic liver disease will be considered for inclusion. Listed patients must meet all of the following inclusion criteria to be eligible for participation in the VITTAL trial:Adult primary liver transplant recipient;Patient listed electively for transplantation;Low to moderate transplant risk candidate, suitable for marginal graft, as assessed by the UHBFT liver transplant listing multidisciplinary team (MDT) meeting (these are usually candidates with low UKELD score, without cardiovascular comorbidities, with good functional and nutrition status, with patent portal vein and with no history of previous major upper abdominal surgery, for example, patients transplanted for liver cancer);There is no lower limit for MELD or UKELD. Upper UKELD is discussed in the exclusion criteria below.

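### The abstract says the trial will determine equivalent patient survival, but the only survival rule tests against 73%, no comparator or margin is set, and the matched comparison does not name 90-day patient survival

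*Protocol article*

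**What the plan says.** The abstract of the protocol article (Methods and analysis) gives the purpose of the design as determining whether rejected livers can be "salvaged and safely transplanted with equivalent outcomes in terms of patient survival". It does not say equivalent to what, or within what margin.

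In the body, primary objective B is narrower: to achieve successful transplantation of previously rejected livers, measured by the proportion of recipients alive at 90 days. Under Sample size justification, the three-stage design will "test the null hypothesis that the mean 90-day patient survival rate will be less than 73% (p≤0.73"), against the alternative that "the 90-day patient survival rate will be at least 88% (p≥0.88"). The target error rates are both 0.2. The trial continues with at least 2 of 3 and at least 8 of 11 survivors, and succeeds with at least 18 of 22. The same section notes that the mean 90-day survival for standard "liver transplants is 93" per cent, but no test uses that figure.

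Under Primary analysis, rates are to be reported with Wilson confidence intervals; no confidence level is given for them. Under Secondary analysis, primary non-function and early allograft dysfunction are to be assessed by "comparing results with a contemporary matched recipient group of patients obtained from a prospectively maintained database", with adjustment for potential confounders.

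**The concern.** To claim equivalent survival, a trial needs a reference rate or group, a margin, and a rule that uses both. Here the null rate is 93 − 73 = 20 points below the quoted standard, and even the desirable rate is 93 − 88 = 5 points below it. Rejecting 73% says only that survival is probably better than a rate the plan itself calls undesirable.

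The abstract is what most readers will see. A trial that meets its success rule could therefore be reported as having answered the abstract's question when the rule never addressed it. The one planned comparison with other recipients does not fill the gap, because the outcomes named for it do not include 90-day patient survival.

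**Working it through.** **Inputs.** Null 0.73, alternative 0.88, target α 0.20, target power 0.80, and standard survival 0.93 (Sample size justification). Boundaries: at least 2 of 3, at least 8 of 11, at least 18 of 22 (same section). Wilson method (Primary analysis). The 95% level is my assumption; the article states 95% only for median survival.

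**1. The plan's own figures.** Let X1 ~ Bin(3, p), X2 ~ Bin(8, p), X3 ~ Bin(11, p), independent. Then

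P(success) = P(X1 ≥ 2, X1+X2 ≥ 8, X1+X2+X3 ≥ 18).

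Exact summation gives 0.234 at p = 0.73 and 0.857 at p = 0.88, against the stated targets of 0.20 and 0.80. The stated rule therefore does not reproduce its targets. With continuation at 9 of 11 the same design would give 0.199 and 0.803. That is a separate discrepancy between the second-stage boundary and the error rates, which must be reconciled. The point here does not rest on it. The results below use the rule as printed.

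**2. What a pass says about the distance from 93%.**

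| True 90-day survival | Points below 93% | P(success) |
|---|---|---|
| 73% | 20 | 0.23 |
| 80% | 13 | 0.51 |
| 83% | 10 | 0.65 |
| 85% | 8 | 0.74 |
| 88% | 5 | 0.86 |
| 93% | 0 | 0.97 |

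At a true 80%, 90-day mortality is 20% against 7% for the quoted standard, and the trial still succeeds about half the time.

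**3. Wilson interval at and near the pass mark** (n = 22, z = 1.96).

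Centre = (p̂ + z²/2n) / (1 + z²/n); half-width = z·√[p̂(1−p̂)/n + z²/4n²] / (1 + z²/n).

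- 18/22 (p̂ = 0.818): 0.771 ± 0.156, giving 61.5% to 92.7%. The upper limit is 0.3 points under 93%, and the lower limit is below 73%.
- 19/22 (p̂ = 0.864): 0.810 ± 0.143, giving 66.7% to 95.3%. This includes 93%.
- 22/22: 85.1% to 100%. Even a perfect result leaves survival about 8 points below 93% within the interval (93 − 85.1 = 7.9).

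Sensitivity at 18/22: the Clopper-Pearson upper limit is 94.8% and the continuity-corrected Wilson upper limit is 94.0%. Both include 93%. None of these intervals adjusts for the interim looks.

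**4. How often the trial passes at exactly 18/22.** The probability is 0.189 at a true 80% and 0.136 at a true 88%. As a share of all successes at 88%, that is 0.136/0.857 = 16%.

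**5. What a matched survival comparison could offer.** Assume 22 trial patients and 44 controls, with survival 88% and 93% (the number of controls is my assumption):

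Half-width = 1.96 × √(0.88×0.12/22 + 0.93×0.07/44) = 1.96 × √(0.00480 + 0.00148) = 0.155, or about 15 to 16 points.

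**The case against.** The strongest reply is that this is one word in an abstract. The body does not repeat the equivalence aim. Objective B speaks of successful transplantation, the 73% and 88% rates and the 0.20 level are stated openly, and the closing Summary claims no equivalence. A 51% chance of success at a true 80% is what a disclosed design between 73% and 88% will produce; it is not an arithmetic error. All of that stands. It makes the fault easy to cure, but the sentence still assigns the design a purpose that the design cannot serve.

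A reader might go further in three ways that the document does not support.

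- *A trial that passes will have shown survival worse than standard.* The interval excludes 93% only at exactly 18/22, only at an assumed 95% level, and by 0.3 points. At 19/22 it does not.
- *The 93% describes unselected recipients and so flatters or penalises the trial.* The article calls it the mean for standard transplants and says no more. The trial does restrict entry ("Low to moderate transplant risk candidate, suitable for marginal graft") and discloses this among its limitations, but the make-up of the group behind the 93% cannot be judged from the text.
- *The matching list is deficient because it omits the trial's recipient criteria.* The article also provides for adjustment for confounders, and how controls are drawn may be set out in a document not shown. Some of the supposed criteria, such as freedom from cardiovascular comorbidity, are given only as what candidates usually look like.

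It can also be said that 90-day graft survival and 12-month patient and graft survival are listed as measures under the graft-function objective, so a generous reading might bring them into the matched comparison. Even that reading does not reach 90-day patient survival.

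**Conclusion.** The point holds as an inconsistency between the stated aim and the design. The article says the trial will determine equivalent patient survival, yet it sets no comparator or margin and tests survival only against 73%. Its matched comparison does not name the primary survival endpoint. Under the printed rule, success has probability 0.51 at a true 80% and 0.65 at a true 83%, so a pass is compatible with survival well short of 93%. Those probabilities are exact for the printed boundaries. The interval result at 18/22 rests on the 95% level and on the Wilson method, and it is a borderline illustration; the conclusion does not depend on it. The matter should be corrected because it governs what may be concluded from a success, but it does not invalidate the test of 73% against 88% as a design.

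**What to change.** 1. Reword the aim in the abstract to 90-day patient survival above the undesirable 73% rate. State that meeting 18/22 is not evidence of equivalence to standard transplantation.
2. Add 90-day patient survival and 90-day graft survival to the planned matched comparison. Report each as a descriptive difference with its interval and with no success criterion attached.
3. State the confidence level for the Wilson intervals, so that what is reported beside the pass mark is fixed in advance.

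The cost is wording plus one more analysis in a matched dataset already planned. The drawback is precision: at about ±15 to 16 points on the assumed numbers, the matched difference will be direct but imprecise. It cannot establish equivalence either, and the report should say so.

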**Ethics and dissemination:**

The protocol was approved by the National Research Ethics Service (London—Dulwich Research Ethics Committee, 16/LO/1056), the Medicines and Healthcare Products Regulatory Agency and is endorsed by the National Health Service Blood and Transplant Research, Innovation and Novel Technologies Advisory Group. The findings of this trial will be disseminated through national and international presentations and peer-reviewed publications.

**Trial registration number:**

NCT02740608; Pre-results.

Strengths and limitations of this studyThe study will answer the question: ‘Can ex situ end ischaemic normothermic machine perfusion safely increase the number of transplantable livers?’The study aims to establish objective liver viability criteria and biomarkers that may enable point-of-care assessment of liver quality.The study has clearly defined criteria characterising the discarded organs.Incorporation of an adaptive three-stage trial design provides opportunities to assess patients’ safety, allowing for early trial termination if necessary.The trial includes low and moderate risk recipients only—the suitability for high-risk recipients will require further testing.

## Introduction

### Liver transplantation

Liver transplantation is a highly successful treatment for end-stage liver disease, fulminant hepatic failure and early-stage primary liver cancer. Deaths from liver disease have soared by 40% in a decade and continue to rise. Liver disease kills 11 000 a year in England and the average age of death from liver disease (59 years) continues to decrease.^1^ Over the past 50 years, transplant techniques and outcomes have greatly improved and 5-year survival rates of 70%–80% mean that transplantation has become the mainstay of treatment for an increasing number of patients with chronic liver disease, metabolic disorders, acute liver failure and malignancy. As such, the demand for donor livers greatly exceeds supply and approximately 20% of patients die while awaiting transplantation.^2^ In Europe, the most common indications for liver transplantation are cirrhosis (68%), malignancy (14%) and acute hepatic failure (8%). The main causes for cirrhosis in Europe are the hepatotropic viruses and alcohol-related liver disease.^3^ Non-alcoholic fatty liver disease is an emergent cause and despite health campaigns, the incidence continues to rise. In the UK, it is predicted that the incidences of end-stage liver disease and hepatocellular carcinoma will increase substantially during the next decade, exacerbating the existing shortage of donor livers.

### The UK liver transplant programme

Between March 2015 and April 2016, there were 1161 new waiting list registrations in the UK, and 878 transplants were carried out. Of the 621 patients on the list as of April 2015, 22% died or were removed from the list (n=135) due to deteriorating health.^4^ This is reflected across other countries to the extent that a patient is now more likely to die within the first 12 months of being listed than the first 12 months’ post-transplant.^5^ Over the past decade, there has been a very modest increase in the use of standard or ‘ideal’ organ donors (those retrieved from young donors following a diagnosis of brain stem death, (DBD)). In response, centres have use donors following circulatory death (DCD) and suboptimal ‘marginal’ or ‘extended criteria’ donors (those of older age, livers with a presence of steatosis, etc).

### Responding to the shortage

There are several ways to respond to the shortage. Organ donation policies are undergoing changes; however, there is a lack of well-controlled scientific evidence on which to base decisions regarding policy-making and opinions are strong and divided. Spain has the highest organ donation rates and operates an opt-out system, however, the rise in rates only started approximately 10 years after the system’s introduction. Wales is the most recent country to go down this route, however unlike in Spain, next of kin consent is still required before patients can become organ donors. More likely, the increased Spanish donation rates are due to a combination of factors—the creation of a transplant coordination network that operates at hospital, regional and national levels, the placement of transplant coordinators at each procurement hospital and the improvement in the quality of information received by the public. Living donation is one potential means to increase the number of liver transplants, using surgical techniques developed for liver resection and ‘liver splitting’ (which uses a single liver for transplantation into two recipients). The major limitations are most patients do not have a willing or suitable living donor and there are concerns about the risks to the healthy donor. The reported risk of donor death is estimated at 0.2% but the risk of serious complications is much higher.^6 7^ Although programmes have had some success in countries without deceased donor programmes, living donor transplantation will be unlikely to have a significant impact on the shortage of donor livers in most countries.

### The use of ‘marginal’ or ‘extended criteria’ donors

As discussed, a rising proportion of transplants are carried out using ‘marginal’ or ‘extended criteria’ grafts, procured from obese or elderly donors with multiple comorbidities.^8^ These livers are significantly more susceptible to cold storage-related ischaemic injury, which increases the risk of graft failure and recipient morbidity and mortality. Reflecting the issues with these suboptimal grafts, in 2014/2015, of 1282 solid organ donors, only 924 (72.1%) livers were deemed suitable for retrieval and only 812 (63.3%) were subsequently transplanted.^9^ The duration of the functional warm ischaemic time (FWIT) is an important determinant of outcome. The recent document ‘Donation After Circulatory Death’ published by a steering group on behalf of the British Transplantation Society and Intensive Care Society suggested that the stand-down time from the onset of functional warm ischaemia for DCD liver transplantation was 30 min (although 20 min is ideal), and that age was an important factor. Because of this, a number of livers will be retrieved from DCDs that fall into the ‘marginal donor’ category and may not go on to be transplanted.^10^

Several donor parameters have been identified as relative risk factors for poor outcome including age, steatosis, DCD donation, split livers and prolonged cold ischaemia time (>12 hours). These were all developed using North American data and formulated into an algorithm known as the Donor Risk Index (DRI) and later validated using European data.^11 12^ The British Transplantation Society have published their own guidelines on the use of donor organs and use criteria in table 1 to distinguish between grafts of varying quality.

**Table 1 T1:** Criteria for donor quality as per British Transplantation Society UK Guidelines for donors after circulatory death

Good livers—all should be used (DBDs and DCDs)	Ideal livers—all should be used (DCDs)	Marginal donors—use selectively (DCDs)	Absolute contraindications to using liver as donor organ
Age<50 Normal LFTs <5 days on ICU Low levels of inotropic support <30% steatosis No active sepsis	Age<50 years Weight<100 kg FWIT<20 min CIT<8 hours <15% steatosis ICU stay<5 days	Age >50 years Weight >100 kg FWIT 20–30 min CIT 8–12 hours >15% steatosis ICU stay >5 days	DCD with macrovesicular steatosis >30% ESLD Acute liver failure Acute liver injury that is not improving

CIT, cold ischaemic time; DBD, donor following brain death; DCD, donor following circulatory death; ESLD, end-stage liver disease; FWIT, functional warm ischaemic time; ICU, intensive care stay; LFTs, liver function tests.

### Organ preservation

The current standard of donor liver preservation is based on static cold storage (SCS).^13^ During SCS, organs are flushed and cooled with specific chilled preservation solutions (University of Wisconsin solution is used most commonly although histidine–tryptophan–ketoglutarate (HTK) solution is also used less widely) and ice is added to the abdominal cavity. After retrieval, the organ is placed in fluid-filled sterile plastic bags for transportation and stored in preservation solution within an ice box until transplantation. Although the available preservation solutions differ in chemical composition, their function is essentially the same. The hypothermia aims to reduce the liver’s metabolic activity and the solution aims to reduce the cellular swelling. This is a consequence of anaerobic metabolism resulting in depletion of ATP stores leading to influx of free calcium and activation of phospholipases.^14^ Cooling the organ slows metabolism approximately 12-fold but cannot prevent its dysfunction and the eventual destruction of cellular integrity. Ischaemia reperfusion is an important factor influencing graft outcome.^15^ The ischaemic phase starts early in the procurement process (swings in blood pressure following brain death or due to the functional warm ischaemic time in non-heart beating donors) and triggers a complex cascade of cellular and molecular events including the release of proinflammatory mediators and chemotaxis of cell types that initiate progressive immunological processes. During the reperfusion phase, ‘the reflow paradox’ causes infiltration of the tissues by leucocytes and cellular injury occurs through a series of pathways that include lipid peroxidation and the creation of reactive oxygen species^16^ The most common manifestation of the ischaemia-reperfusion process is delayed graft function, which is the inability of the organ to fulfil the physiological needs of the recipient and is associated with graft failure, retransplantation and death.^17^Static cold storage therefore is unable to reverse the injury sustained during donor death and procurement, causes injury due to the cooling process, limits the preservation time and prevents physiological assessment prior to transplantation.

